#### Exclusion

Families will be excluded from the trial if the parent(s) is unavailable to take part in an intervention (for example, because of death, unknown whereabouts or long-term imprisonment).

If a family has been randomised previously but became ineligible without being exposed to either of the study interventions, then the family may be randomised again, should they become eligible at a later date.

### Who will take informed consent? {26a}

Trial recruitment coordinators (experienced social workers trained in conducting consent interviews) will be notified of a newly eligible (or potentially eligible) family via social workers or designated members of the legal team in each local authority area. They will confirm that birth families have received information sheets and videos about the trial and have assented to be approached by a recruitment coordinator. If so, we will arrange a meeting to discuss trial participation, answer any questions and, if proceeding, go through the informed written consent process. Subsequent meetings can be arranged if birth parents would like more time to decide about participation. Consent can be taken remotely in extenuating circumstances.

If parents agree to participate in the study, foster/kinship carers will be contacted by one of the research team to discuss their participation in the study and take consent.

### Additional consent provisions for collection and use of participant data and biological specimens {26b}

We take consent to access routinely collected health and social work data about the child and parent. Any specific requests for routine data from central sources (e.g. NHS or legal system routine data) will require a separate application and be governed under information governance legislation by the relevant bodies. The data will be used to monitor safety throughout the trial, to examine the representativeness of the trial sample, to augment the planned health economics analysis and to monitor current placements of children in the study to enhance retention rates at follow-up.

Data contributing to our time to permanent placement secondary outcome measure are gathered, blind to arm of trial, from social work and legal system records. These data include dates and recommendations of the parenting capacity assessment received, dates and recommendations made at permanence hearings, placement details and legal orders after permanence decisions were made.

In addition, routine data will be used as part of the process evaluation, for example to examine how the social care and legal context is related to children’s journeys through placement and to their mental health. This is described in a separate process evaluation protocol paper [29].

## Interventions

### Explanation for the choice of comparators {6b}

Families not randomised to NIM will receive services as usual (SAU), i.e. the assessment and intervention that social services and others normally implement when children are removed from parental care. SAU includes regular contact with families by a social worker Case Manager, assessment of family relationships and signposting of families towards existing services. Case Management was described and found to be effective in a randomised controlled trial conducted in the USA [28]. It is important to note that the Case Management evaluated in that study was similar to the minimum service routinely offered by social work departments across the UK, since “local authorities have a duty to safeguard…children … and…[provide] a range and level of services appropriate to the children’s needs” [30, 31]. Such Case Management services are not routinely available in the USA [32]. In Scottish and English sites, social workers will continue to assess the family, help to engage them with support/clinical services and have their services scrutinised intermittently in government-mandated inspections. In addition, during the trial, there will be regular discussions about service delivery with all local authority colleagues in regular local study Steering Groups and liaison with professionals from other key services relevant to children’s care placements [33].

We anticipate that the nature and intensity of services as usual will vary across different geographical areas and across time during the trial. The Glasgow version of SAU—run by the Family Assessment and Contact Service (FACS)—is an ideal attention control for NIM because it also offers a relationship-based assessment of the parental capacity to care for the child, but has a social work ethos, including more naturalistic observations of the family and unstructured assessments of case files. It does not contain an infant mental health treatment component. In Renfrewshire, the Family Assessment and Contact Team (FACT) offers an assessment using a similar framework. Current SAU in the relevant London boroughs are relatively sophisticated compared to many areas of the UK because of their close relationship to South London and Maudsley Trust (SLaM) which is a partner in this collaboration. For example, state-of-the-art interventions for foster carers such as Dozier’s Attachment and Biobehavioural Catch-up (http://abcintervention.com/) are available for some families. The London Boroughs involved in the trial adopt one of three different methods for assessing families. The first is an assessment delivered by a specialist team within the borough who will offer an assessment of parenting capacity (as with the Glasgow and Renfrewshire models). The second is an assessment carried out by the allocated social worker with additional services (e.g. child and adolescent mental health services) engaged if the social worker deems this to be required. The third is a specialist assessment carried out by an independent social worker/psychologist/psychiatrist. All three methods of assessment must be undertaken within 26 weeks as per the expectations set out by the Judiciary in London. Further exploration of the detailed nature of SAU in London is a key objective of qualitative mapping and modelling we are currently undertaking and is included as part of the trial process evaluation. The heterogeneous nature of services as usual across the Local Authorities feeding into the London and Glasgow sites is seen as a strength in that it will allow for a more detailed exploration of what works, for whom and why. In contrast with NIM, the systems of care that comprise SAU have developed iteratively, borne out of local authority contexts and processes (constrained by local statutory guidance), and have never been formally evaluated.

### Intervention description {11a}

The experimental intervention is NIM, which aims to improve the mental health of young, maltreated children. It has a US evidence-base, although not derived from an RCT [34]. NIM is an intensive, targeted, individualised, family-based intervention that aims to offer assessment and trial-of-treatment for the birth family and make timely recommendations for rehabilitation back to the birth home or adoption.

We have found only one intervention, NIM, that uses an infant mental health approach aiming to improve the quality of permanent placement decisions so that children can experience appropriate nurturing care as early in life as possible [34]. The Tulane Infant Team, who developed NIM, assesses the mental health and relationship quality of every maltreated child under 5 years of age on reception into care. A tailored intervention is then offered to each family aiming to improve parent-child relationships and child mental health. These assessments and the degree of change achieved through intervention inform recommendations to the legal system about the permanent future care of the child. Where significant change has been achieved, it is recommended that children are rehabilitated back to the birth family. If not, the recommendation is adoption. An evaluation of the 4 years prior to, compared with the 4 years after, the introduction of the NIM in the US suggested that the programme effects an increased rate of adoption and, for those returned to birth families, a risk reduction of more than 50% in repeated maltreatment for both that child and subsequent siblings [34]. A follow-up of children several years after exposure to NIM in infancy has shown that on many mental health measures graduates of NIM, whether adopted or rehabilitated to birth families, differed only slightly from the general population [35]. These are apparently remarkable findings, when the high rates of psychopathology in populations of children in care are considered [36] but should be viewed with caution because these studies did not involve randomisation or control interventions and it is possible that other factors contributed to these outcomes. In particular, the Adoption and Safe Families Act, which placed tighter legal guidelines around judicial decision-making about young children in care, came into force just after the NIM service started in Louisiana [37] and it is quite possible that this could account for the improvement in children’s outcomes. In addition, the extent to which these findings could be generalised to a UK context is not known: in Louisiana, there is very little child welfare social work offered to families in the community [32] so NIM has never been tested against the Case Management that is routinely offered as part of UK social care.

The NIM intervention is as follows: a multidisciplinary infant mental health team comprising psychologists, a psychiatrist, other therapists and social workers assesses the mental health and relationship quality of children under 5 years of age upon reception into care. The assessment, which involves each actual and potential caregiver, is manualised and standardised and uses structured interviews, self-report measures and observations. A multidisciplinary meeting is then held to decide if it is appropriate to proceed to a tailored trial-of-treatment. Wherever possible, treatment is offered to each family, drawing on a small range of relationship-based therapeutic techniques all of which comply with the recommendations of a meta-analysis that examined ways of improving parental sensitivity [38]. Parents are also referred as required to other agencies for help with substance misuse, mental health issues or intra-familial violence. These assessments, and the degree of change achieved during the trial-of-treatment, inform recommendations to the legal system about the permanent future care of the child. The aim is to have “the best outcome possible for [the] particular child” ([name], personal communication, 2014), be this a recommendation of rehabilitation to birth family or adoption [34]. Where significant change has been achieved, children are rehabilitated back to the birth family. If not, the recommendation is adoption. Throughout the time that birth families are receiving the intensive intervention, the child remains in a nurturing placement with foster carers who are ideally willing to adopt the child if necessary, although the feasibility trial has shown that foster carers being dually registered as adopters is rare in the UK [39].

In this definitive trial, NIM will be delivered by the Glasgow Infant and Family Team (GIFT) and the London Infant Family Team (LIFT).

A logic model for NIM (Fig. 1) was developed in collaboration with the developers (Professors [name] and [name]) prior to the feasibility RCT and may be modified, as a result of process evaluation findings, prior to any roll-out of NIM should it be proven cost-effective.

**Fig. 1 Fig1:**
[figure not shown]
The logic model, NIM

### Modifications

Two modifications of NIM have become necessary for the definitive trial.

#### Modification to be used in responding to unanticipated service demands

During the period of randomisation-before-consent, the NIM team had significant problems with capacity. This happened again after the first COVID lockdown when social services were cut back. We therefore consulted with the Tulane team for advice on how they had coped with surges in demand. One such surge in demand occurred after Hurricane Katrina, in 2005, when the Tulane Infant Team experienced a 50% increase in referrals. Their advice, based on this experience, was to offer more limited infant mental health input to the entire target population wherever possible. With their guidance (sought by email and phone, and captured for the process evaluation in a focus group in January 2016), the NIM team developed what was termed “NIM light”, for use only during situations of sudden increase in demand. The components of NIM light were:
Infant mental health-focussed consultation to social work Case ManagersAnd/or strategic consultation with service managers to prioritise where NIM can have the most impact for those children on any waiting list—again with an infant mental health lensAnd/or provision of NIM assessment (possibly truncated, e.g. if lack of engagement) without provision of trial-of-treatment (e.g. if the family had demonstrated by non-attendance that unlikely to be motivated towards treatment)A further modification was to use an abbreviated assessment, e.g. with abbreviated WMCI and Crowell

Since the study is using an intention-to-treat approach to analysis, we will carefully log those families who received NIM light, rather than NIM (including the amount of NIM they received) as well as any families who, for whatever reason, were randomised to NIM but did not receive the intervention at all.

An additional UK-specific challenge is that routine infant mental health services for babies and pre-school children do not exist in the UK so that, if the NIM teams identify mental health problems in children involved in their trial-of-treatment, there may be no relevant service to refer the child and family on to, which has contributed to slow throughput through NIM. We have addressed this, in Glasgow, by instituting a small multi-agency group called the “Traffic Light Operational Group” that reviews progress through the GIFT team using a traffic-light system which flags families as “red”, “amber” or “green” according to their progress through key points in the NIM timeline. In London, this role is taken by the Judiciary who mandate timescales by which time LIFT must report to them. Should the process evaluation suggest it, we may recommend that NIM light, the TLOG and/or Judicial mandating of timelines become part of the service specification for any future roll-out of NIM in the UK social care and health systems.

#### Modification for the COVID-19 pandemic

Although parenting capacity assessments (by either NIM or services as usual) were deemed to be essential services during the COVID-19 pandemic, referrals of new cases to both arms of the trial had to cease between March and July 2020 because national lockdown restrictions precluded birth families from having contact with their children. Since the legal systems in both England and Scotland regarded observation of live contact between parents and children to be a crucial part of judicial decision-making about children’s care placements, little intervention from either NIM or SAU was possible during these dates. Gradually, each local authority in the study, as well as the NSPCC, developed safe systems for birth families to meet their children and have these contacts observed. Necessary modifications included workers being designated as “essential workers”, availability of Personal Protective Equipment, availability of rooms large enough for safe social distancing to take place and additional cleaning of premises. In tandem, there was rapid development of systems for some contacts and for the standardised assessments and treatments offered as part of NIM to be delivered remotely. Since April 2020, both NIM and services as usual have offered a mix of face-to-face and remote assessments. The challenges involved in service delivery during the pandemic, and the quality of this service delivery, are being examined as part of the process and health economic evaluations. Sensitivity analyses will be conducted to examine any quantitative impact on trial outcomes.

## Criteria for discontinuing or modifying allocated interventions {11b}

If there is a sudden surge in demand for NIM, then, if multi-agency partners agree, NIM light may be offered (see above) to reduce the waiting list and ensure that all of the target population are offered a service.

### Strategies to improve adherence to interventions {11c}

To optimise adherence to NIM, both the GIFT and LIFT teams were trained directly by members of the Tulane Infant Team. GIFT was offered weekly video-conferencing with [name] and/or [name] for the first 2 years they were operational. Once the LIFT team were operational, they received regular video-conferencing supervision from both the Tulane Infant Team and the GIFT team who, by this time, were expert in delivering NIM. During the feasibility trial, [name] and [name] scrutinised 18 anonymised and randomly selected reports from the GIFT team with a view to instituting any necessary quality improvements and this will continue during the definitive trial. In addition, in September 2018, we held an away day with members of the Tulane Infant Mental Health Team, GIFT and LIFT to establish, together, what the core components of NIM are—and this was recorded as a focus group to be reported as part of the process evaluation.

To maximise families’ adherence to NIM, families are asked to sign a service agreement prior to beginning the intervention and the importance of attendance for reporting to the legal system is emphasised. Similar processes are conducted for services as usual although these are more formal in England (where social workers are formally tasked to report back to the court by a certain date) than in Scotland where reporting requirements to the Children’s Hearing System are more variable.

### Relevant concomitant care permitted or prohibited during the trial {11d}

There are no restrictions on concomitant care.

### Provisions for post-trial care {30}

There are no provisions for post-trial care other than services to which the NIM and SAU workers decide to refer families.

### Outcomes {12}

The primary outcome is child mental health at 2.5 years post-randomisation (see below).

Secondary outcomes, at 2.5 years post-randomisation, are:
Time taken to reach a permanent placement (TTPP) (be that adoption or return to birth family without social work supervision)Parent/carer-child relationship qualityCost-effectiveness

#### Primary outcome measure

Our primary outcome is child mental health, and our primary outcome measure is the Strengths and Difficulties Questionnaire (SDQ). This is a brief behavioural screening questionnaire for 2–16-year-olds (therefore always appropriate at time 3 even if the child entered the study near birth), completed by the primary caregiver (i.e. the caregiver with whom the child is living), with 25 items in 5 subscales: emotional symptoms, conduct problems, hyperactivity/inattention, peer relationship problems and prosocial behaviour [40]. It is sensitive to change in intervention studies, and effect sizes are moderate to large [41–43]. Our review of the literature suggests that SDQ is the most widely used and well-validated measure of mental health in children.

#### Secondary outcome measures

These address the other key components of our NIM logic model (Fig. 1).
Parent- or carer-child relationship. This will be measured using the Parent-Infant Global Assessment Scale (PIR-GAS) [44].Time between first care episode and permanent placement decision (adoption or rehabilitation). This will be determined through scrutiny of routinely held social work data.

There is no risk of unblinding with either of these secondary outcome measures as they are rated/entered independently from the research team.

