### Implementation {16c}

Participants are enrolled on the randomisation system by recruitment coordinators. Recruitment coordinators, trial managers and nominated contacts per site and per arms of trial are automatically informed of the intervention allocation by email. Recruitment coordinators inform the social worker managing the families’ case of arm of trial, and the social worker will then work with the family to manage access to the arm of trial.

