## Assignment of interventions: blinding

### Who will be blinded {17a}

The study is single blind. Participants will be aware to which arm of trial they have been allocated. Researchers and statisticians will not. For questionnaire and interview measures, we have incorporated a system whereby the research assistants have a script that they use as families are invited to assessments that aims to ensure they do not reveal intervention allocation (e.g. by stating the location at which parenting capacity assessments were conducted). Following assessment visits, research assistants state which intervention they think the family were attending so that, at the end of the study, we can assess the degree to which these blinding measures were successful. Parenting quality assessments (PIR-GAS) and Time to Permanent Placement are fully blinded since PIR-GAS is rated by individuals who have no access to group allocation and TTPP through examination of social work data, again by individuals with no access to group allocation.

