### Adverse event reporting and harms {22}

To ensure that serious adverse events relevant to the trial are captured, the study team will review participants’ case notes on a six-monthly basis for the presence of serious adverse events. Deaths as recorded in routinely available health data in Scotland will also be examined. All SAEs arising during the trial will be recorded as soon as reasonably practicable after the site first becomes aware of the event.

Many participants and their birth parents taking part in the trial will have complex medical and mental health histories. Therefore, many adverse events and serious adverse events would be expected to occur within the participant group irrespective of their involvement within the study. These expected events do not necessarily require reporting to the Research Ethics Committee as serious adverse events but will be monitored by the trial team in relation to differential rates across trial arms, via the usual health and social care processes to ensure participant safety, and details recorded in a log. Their relatedness will be assessed by the chief investigator and, 6 monthly, by a small panel of experts (including a consultant paediatrician). The Data Monitoring and Ethics Committee (DMEC) will review these six-monthly.

Any SAE occurring to a research participant (or, in the case of deaths, also, their birth parent) where in the opinion of the chief investigator (CI), the panel of experts or the DMEC, the event was “Related”—that is, it resulted from the administration of any of the research or intervention procedures, and “Unexpected”—that is, the type of event is not an expected occurrence, will be reported by the Pharmacovigilance office to the Research Ethics Committee that approved the trial.

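### Time to permanent placement is declared free of unblinding risk, but it is extracted from records likely to disclose the arm

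*Protocol article*

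**What the plan says.** Under Secondary outcome measures, the article says of PIR-GAS and TTPP: "There is no risk of unblinding with either of these secondary outcome measures as they are rated/entered independently from the research team". Who will be blinded {17a} repeats the point and calls both measures fully blinded. For TTPP the reason given is that the people examining the social work data cannot see group allocation.

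The section on additional consent provisions {26b} describes the TTPP data: "Data contributing to our time to permanent placement secondary outcome measure are gathered, blind to arm of trial, from social work and legal system records". It then lists the contents: "These data include dates and recommendations of the parenting capacity assessment received, dates and recommendations made at permanence hearings", followed by placement details and legal orders.

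For the questionnaire and interview measures, {17a} gives research assistants a script so that families do not reveal their allocation, "e.g. by stating the location at which parenting capacity assessments were conducted". After each visit the assistants also record which arm they think the family is in.

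On harms, {22} says that expected events "will be monitored by the trial team in relation to differential rates across trial arms". Section {17a} says that researchers and statisticians are unaware of allocation. Section {17b} allows independent members of the Data Monitoring and Ethics Committee (DMEC) to be unblinded, with discussion confined to closed meetings. Implementation {16c} says that recruitment coordinators, "trial managers and nominated contacts per site and per arms of trial are automatically informed of the intervention allocation by email".

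**The concern.** Keeping the allocation list from extractors does not blind them if the records they read show the arm. The parenting capacity assessment is part of what differs between arms, so a case file that contains it is a likely source of disclosure. The article guards against this clue when research assistants meet families, but declares no risk when extractors read the files.

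TTPP is a named secondary outcome and serves one of the three secondary objectives. If extractors can tell the arm, any judgement about which event counts as permanence could be affected. Arm guesses are described only for research assistants, so a failure of blinding here would go unnoticed. The trial report would then carry a claim of complete blinding that the procedures described do not secure.

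**Working it through.** No figure is stated on this point and no arithmetic applies. The check sets the sections side by side.

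1. **What the claim rests on.** Secondary outcome measures relies on independence from the research team. {17a} relies on extractors having no access to group allocation. Both describe who the extractors are and what list they cannot see. Neither limits what the records show them.

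2. **What the extractors work from.** {26b} names social work and legal records as the source and includes dates and recommendations of the parenting capacity assessment.

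3. **Whether that assessment differs by arm.** Under Intervention description {11a}, the New Orleans Intervention Model (NIM) is delivered by the Glasgow Infant and Family Team and the London Infant Family Team. Under Explanation for the choice of comparators {6b}, services as usual are delivered by others: the Family Assessment and Contact Service in Glasgow, the Family Assessment and Contact Team in Renfrewshire, and in London a borough specialist team, the allocated social worker or an independent assessor. The provider therefore indicates the arm.

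4. **Whether the records are likely to show it.** Under {16c} the social worker managing the case is told the arm and arranges access to it, so entries in the case record that identify the arm are to be expected. {17a} itself treats the place of assessment as revealing.

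5. **Whether anything offsets this.** {26b} asserts that the data are gathered blind to arm, but the article describes no masking or redaction of records and no arm guess by extractors.

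6. **Whether knowledge of the arm could matter.** Outcomes {12} times TTPP to reaching a permanent placement, which for a return home means without social work supervision. Secondary outcome measures times it from the first care episode to the placement decision. {26b} lists hearings, placements and legal orders as separate items. The dates are recorded, but choosing the qualifying event leaves some room for judgement.

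7. **Harms.** {22} gives monitoring of rates across arms to the trial team without naming members. {17a} blinds researchers and statisticians. {16c} informs trial managers and recruitment coordinators, and {5d} counts both as part of the research team. Members who already know the allocation could do the monitoring by arm, but the article does not say that they do, or that the results are kept from the others.

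**The case against.** The strongest reply is that {26b} lists only dates and recommendations, not the provider or the place of assessment, and says directly that collection is blind. A recommendation of return home or adoption can arise in either arm and does not identify it. The location example in {17a} concerns families talking to research assistants, not fields in a file. Operating procedures for each measure {18a} and a data management plan {19} are promised, and masking could be set out there. Most of this stands as a limit on strength: disclosure is inferred, and a reader who concludes that the extractors are shown to be unblinded goes beyond the text. It does not rescue the absolute claim. The reasons the article gives would not produce zero risk, and the point challenges that affirmative statement, not an omitted detail.

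The differing definitions of TTPP are a separate issue that changing the blinding text will not settle. They matter here only because they leave room for judgement.

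Three further readings are tempting and not supported. The challenged sentence also covers PIR-GAS, but no problem is shown for that measure. A reader might infer that relatedness of adverse events is judged by people who see rates by arm. {22} gives relatedness to the chief investigator and an expert panel, does not say that either sees those rates, and the chief investigator is not on the list of those emailed in {16c}. Nor is the harms wording a proven breach: {16c} openly unblinds some team members, and {17b} governs unblinding of DMEC members without expressly covering every comparison by arm.

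**Conclusion.** The point holds for TTPP: the statements that it carries no unblinding risk and is fully blinded are not supported by the article's own account of the data. The conclusion rests on two assumptions: that the records from which the assessment's dates and recommendations are taken also show who carried it out or where, and that no masking is applied beyond what is described. The size and direction of any bias cannot be estimated from the document. It may be small where hearing and order dates are formally recorded. The effect is confined to one secondary outcome and to the accuracy of the reported blinding status.

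The harms wording is a separate and minor inconsistency that needs reconciling.

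**What to change.** - **Wording.** For TTPP only, replace the claims of no risk and full blinding with a statement that extractors are not given the allocation but may meet clues to it in the records.
- **Order of extraction.** Take the permanence date from the hearing, placement and legal-order fields and lock it before the assessment fields are opened. This reduces the risk but may not remove it, because hearing records may mention the assessment.
- **Check of blinding.** Have each extractor record a guess of arm, as research assistants already do, and report the results alongside theirs.
- **Harms (minor).** Send event rates by arm to the closed DMEC report, or restrict them to named members already informed under {16c}. Keep them from blinded researchers and statisticians. The DMEC already reviews these events every six months, so the route exists.

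The cost is a reordered extraction form, one extra field, slightly more handling and a change to report routing. No added staff and no change for families are needed.
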